### Trial products, storage and accountability

The product to be tested in the trial is azithromycin 100 mg dispersible tablets, which are a commercial product and were obtained for the trial as a donation from Cipla Pharmaceuticals, Mumbai, India. Azithromycin is approved for use in children in Uganda where the trial will take place. Cipla Ltd is fully GMP compliant and has provided full certificates for the manufacture of these products. Azithromycin will be stored at room temperature and not exceeding 30°C (86°F). It will be stored in these conditions for three years as packaged. The trial coordinator at the site will maintain accountability logs for the antibiotic intervention (standard and interventional). These will be kept securely until verified by the external monitor’s visit.

## Sub-studies

### PKPD study

For PK analysis, model-based sampling strategies will enable the description of both intra- and inter-patient variability. A maximum of 3x 0.2ml samples will be taken from each subject on two occasions between day one to five around meaningful time points to describe the PK throughout a dosing interval plus one sample at follow up on day seven to determine the elimination of azithromycin after end of treatment (a total of seven samples per patient). In the first year we will develop highly sensitive bioanalytical assays using ultra performance liquid chromatography coupled with tandem mass spectrometry (UPLC-MS) for determination of azithromycin in stored microvolumes of plasma (analysis performed at Radboud University, Nijmegen). 

Initially a population PK model will be developed for azithromycin and will investigate possible covariates for its PK. This will be followed by an investigation of the relationship between plasma PK and PD using the developed PK model, known MIC-values since the area under the curve (AUC):MIC ratio is the pharmacodynamic driver for azithromycin
^
16,
30
^ and the treatment outcomes (changes in CRP at day three and microbiologic cure and/or mortality at day seven). Based on Monte Carlo simulations, we expect that all dose groups should reach the population reference target (adult) AUC24h of at least 3.4 h*mg/L
^
24
^, although there are no data on absorption in severe malaria, which is characterised by impaired gut function
^
25
^, hence the need for this pilot. The different doses in 105 children provides variability in exposure so that we identify whether all doses are in the flat part of the exposure-response curve, in which case the lowest dose will be chosen. Other secondary endpoints include mortality at 48 hours, length of hospital stay (days), re-hospitalisation and other adverse events. Quality-control of stored bacterial isolates, non-culture (molecular) assessment of bacterial infection including the determination of MIC to inform PKPD studies will be batch-processed at KWTRP, Kenya.

### Biomarker and gut barrier function

In 105 trial participants and 50 children with controls (severe malaria without Teule criteria) we plan to investigate from admission samples the utility of a range of potential biomarkers including CRP, PCT
^
31,
32
^ and endotoxin
^
25
^, to identify whether any of the above markers, alone or in combination, can predict which at-risk children with severe malaria have bacterial co-infections to improve the sensitivity of clinical/laboratory criteria and enable antimicrobial therapy to be further targeted. We will investigate associations between pathological concentrations of these markers and clinical, parasitological and microbiological data in cases (meeting Teule criteria) and controls (not meeting Teule criteria) to test their accuracy for stratification in the main trial. The samples will also allow us to analyse markers of gut barrier dysfunction – a requisite for bacteraemia (intestinal fatty acid binding protein (I-FABP) and the ileal-bile acid binding protein (I-BABP) and establish whether these can accurately predict children with blood-culture proven bacteraemia alone or in combination with clinical criteria/RDTs. In addition, we will analyse the peripheral blood mononuclear cell transcriptome in a subset of children with and without bacterial co-infection to verify the significant changes in transcriptome we observed in a small pilot study of children with malaria and bacterial co-infection compared to children with malaria alone and to confirm observed changes on the cellular level in a second set of children
^
33
^. We will investigate whether changes in gene expression profile can be translated into rapid and affordable biological tests predicting children with bacterial co-infection with high specificity and sensitivity. This later analysis is subject to additional funding.

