### Bacterial co-Infection in severe malaria

We conducted a systematic review in 2013 examining studies among children with malaria admitted to hospitals or outpatient clinics in sub-Saharan Africa reporting invasive bacterial infection (IBI)
^
9
^. We identified a total of 25 studies across 11 African countries which fulfilled the inclusion criteria. These comprised of 20 cohort analyses, two randomised controlled trials and three prospective epidemiological studies. We initially compared the prevalence of IBI in 20,889 children who were hospitalised with all-severity malaria to 27,641 children hospitalised with a non-malarial febrile illness. The mean prevalence of IBI was 5.58 (95% CI 5.5 to 5.66%) in children with malaria and 7.77% (95% CI 7.72 to 7.83%) in non-malaria illness. In the meta-analysis involving 10 studies (n=7,208) of children with severe malaria the mean prevalence of IBI was 6.4% (95% confidence interval (CI) 5.81 to 6.98%). Ten of the 25 studies reported mortality stratified by bacterial infection status. Case fatality was higher at 81 of 336, 24.1% (95% CI 18.9 to 29.4) in children with malaria/IBI co-infection compared to 585 of 5,760, 10.2% (95% CI 9.3 to 10.98) with malaria alone. In seven of 14 hospital studies, NTS was the commonest isolate and one other study listed enteric Gram-negative organisms as the most common isolates in malaria-infected children
^
9
^. Thus, enteric Gram-negative organisms, and NTS in particular, cause the vast majority of bacteraemia co-infections
^
9
^. Moreover, the poor sensitivity of blood cultures (due to low blood volumes in children and previous antibiotic use) means that the true prevalence of bacteraemia co-infection is likely to be significantly higher and ‘nosocomial bacteraemia’ will be acquired in a further 2–3.5% of children receiving a transfusion (commonly prescribed in severe malaria) due to poor quality.

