### Credibility: can antibiotics be targeted?

A major legitimate concern is whether future management guidelines can be implemented which try to reduce the overuse of antibiotics where microbiology services are poor or non-existent, thus an approach to targeting only those with IBI is not feasible in much of Africa. Within the context of this study and to inform a future trial, we aim to investigate approaches (that may be generalizable in future) to targeting antibiotics. We propose to use (i) simple clinical criteria: proposed by Nadjm
*et al.*
^
11
^, the Teule criteria identifies 85% of malaria cases with culture-proven bacteraemia: a pathogen was isolated from 20% children meeting these criteria. Simple and objective criteria identifying those at risk would be more generalizable outside research centres and would be validated in this study. (ii) Potential biomarkers: even when quality-controlled blood-culture facilities are available, low sensitivity (due to frequent pre-hospital antibiotic therapy, low culture volumes from children and low bacterial density) and long times to culture-positivity (typically two-three days) mean that alternative approaches for identifying concurrent gram-negative bacteraemia would be highly valuable.

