### Controls

The control cohort of children (n=50) are those hospitalised with severe malaria but not meeting Teule criteria (i.e., low risk of bacterial co-infection) whose parents are willing/able to provide consent.

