## Sampling

### Sample size determination

A formal sample size was not calculated. Phase I/II trials are an important step in the assessment of new or existing interventions providing the first data on the feasibility of using a product in a new application. They assess the effect of products (how well they work), and the side effects they may have. They are not usually designed to compare superiority of different products or interventions.

The aim is to generate pilot efficacy data on the optimal azithromycin dose for children with severe malaria, which will inform the design of a later larger Phase III trial. The numbers required to address the trial objectives are therefore balanced against the exposure of children in these settings to a therapeutic intervention (dose) for which there are limited data to date.

The overall sample size for the trial will be 105 children randomised 1:1:1 to receive 10, 15 or 20mg/kg azithromycin (based on weight-bands). This is sufficient for the PKPD sampling and modelling to determine an optimal dose in children with severe malaria using change in CRP at 72 hours, and microbiological cure (seven-day) alone and with seven-day survival. This is under the assumption that 20% of enrolled children (meeting Teule severity criteria) will have bacteraemia and that 80% of these infections will be caused by NTS or other enteric gram-negative organisms based on previous research. 

Based on Monte Carlo simulations, we expect that all dose groups should reach the population reference target (adult) AUC24h of at least 3.4 h*mg/L
^
24
^, although there are no data on absorption in severe malaria, which is characterised by impaired gut function
^
25
^, hence the need for this pilot. Along with the 105 children with Teule criteria we will enrol 50 children meeting other inclusion criteria but without Teule criteria (and without any exclusion criteria) into the control group.

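### The biomarker sub-study aims to raise sensitivity, but on the protocol's figures its 50 controls are expected to include only about 0.66 bacteraemic children, too few to estimate a gain over the Teule criteria

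*Protocol article*

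**What the plan says.** Under Biomarker and gut barrier function, the protocol article plans to test admission CRP, procalcitonin and endotoxin in the 105 trial participants and 50 controls, to see whether markers, singly or jointly, "can predict which at-risk children with severe malaria have bacterial co-infections to improve the sensitivity of clinical/laboratory criteria". The same sentence adds a second purpose, closer targeting of antimicrobial treatment. Marker accuracy is to be examined in cases and controls.

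Hypothesis 2 and specific objective (iii) fix culture-proven bacteraemia as the condition to be identified and set the comparison against the control cohort. The Abstract and Discussion describe that comparison too. The Controls section says: "The control cohort of children (n=50) are those hospitalised with severe malaria but not meeting Teule criteria".

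Three figures bear on how much bacteraemia each group will hold:
- Credibility: can antibiotics be targeted? states that "the Teule criteria identifies 85% of malaria cases with culture-proven bacteraemia: a pathogen was isolated from 20% children meeting these criteria".
- Sample size determination carries the second of these figures forward: "This is under the assumption that 20% of enrolled children (meeting Teule severity criteria) will have bacteraemia".
- Bacterial co-Infection in severe malaria reports, from 10 studies, that in "children with severe malaria the mean prevalence of IBI was 6.4% (95% confidence interval (CI) 5.81 to 6.98"%.

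The article does not justify the number 50 or say how many bacteraemic controls are expected.

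**The concern.** A marker can be combined with the Teule criteria in two ways. Requiring the marker as well as the criteria can only keep or lower sensitivity, and what it may improve is specificity and positive predictive value. Accepting the marker as an alternative to the criteria can raise sensitivity, but only by picking up bacteraemic children who fail them. More generally, any rule more sensitive than Teule must detect some Teule-negative bacteraemia. In this study every such child would be a control, and the controls are recruited because their risk is low.

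Two things are at stake. First, the Discussion foresees a Phase III stratum comparing standard of care with no antibiotics in children at minimal risk, with risk possibly set by the Teule criteria and informed by this pilot. Bacteraemia missed by the criteria matters directly for that stratum. Second, cases and controls differ systematically in clinical presentation. If accuracy were judged by contrasting bacteraemic cases with controls, a marker could look good partly because it tracks Teule status rather than bacteraemia.

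**Working it through.** The article gives no calculation for the 50 controls, so there is no stated figure to reproduce.

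**Inputs from the article**
- Sensitivity of the Teule criteria for culture-proven bacteraemia: Se = 0.85.
- Bacteraemia among Teule-positive children: PPV = 0.20.
- Prevalence in severe malaria: p = 0.064 (95% CI 0.0581 to 0.0698). For all-severity malaria: "The mean prevalence of IBI was 5.58 (95% CI 5.5 to 5.66%) in children with malaria".
- 105 cases and 50 controls.

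**Expected bacteraemic controls**
1. Teule-positive share: f = Se × p / PPV = 0.85 × 0.064 / 0.20 = 0.272.
2. Bacteraemia rate in Teule-negative children: r = (1 − Se) × p / (1 − f) = 0.0096 / 0.728 = 0.0132.
3. Expected among 50 controls: 50 × 0.0132 = 0.66.
4. P(none) = (1 − 0.0132)^50 = 51%; P(at least one) = 49%; P(two or more) = 14%.

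**Dependence on prevalence, with Se and PPV held fixed**

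| p | Source | Expected in 50 | P(none) | P(two or more) |
|---|---|---|---|---|
| 5.58% | article, all-severity malaria | 0.55 | 58% | 10% |
| 5.81% | article, lower limit | 0.58 | 56% | 11% |
| 6.4% | article, severe malaria | 0.66 | 51% | 14% |
| 6.98% | article, upper limit | 0.74 | 47% | 17% |
| 10% | assumption | 1.30 | 27% | 38% |
| 15% | assumption | 3.10 | 4% | 83% |

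The expected count reaches 1 only at p = 8.5% or more. If instead culture misses a constant fraction and all rates scale up together, f is unchanged. Doubling the rates then gives 2 × 0.66 = 1.3.

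**What so few children could show**

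If the marker is accepted as an alternative to the criteria, combined sensitivity is 0.85 + 0.15 × s, where s is the marker's sensitivity in bacteraemic children the criteria miss. The gain is 0.15 × s.
- One missed child, detected: exact 95% CI for s is 2.5% to 100%, a gain of 0.4 to 15 percentage points.
- Three missed children, all detected: 29% to 100%, a gain of about 4 to 15 points.

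For scale, expecting 10 missed bacteraemias at r = 1.32% would take about 759 Teule-negative children.

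**What the cases can show**

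Expected bacteraemic cases: 105 × 0.20 = 21, leaving 84 without. A marker positive in 19 of 21 has an exact 95% CI of 70% to 99%; 18 of 21 gives 64% to 97%. A marker negative in 76 of 84 gives a specificity CI of 82% to 96%.

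**Effect of pooling**

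Controls are under-sampled. In natural proportion, 105 Teule-positive children would be accompanied by 105 × 0.728 / 0.272 = 281 Teule-negative children, not 50. In the pooled enrolled sample the apparent Teule sensitivity would be 21 / (21 + 0.66) = 97%, against the cited 85%.

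**The case against.** The strongest counter-argument is about wording. The sentence speaks of at-risk children and of clinical and laboratory criteria, without naming the Teule criteria. Where the article complains of low sensitivity it means blood culture, and it plans molecular detection on stored blood. Finding infection that culture misses could be explored within the 105 cases and needs no Teule-negative bacteraemia. This has weight as a reading of one phrase. It does not remove the problem, because the hypotheses and specific objectives name culture-proven bacteraemia as the target and the control cohort as the comparison. The ambiguity should be resolved in the text.

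Other objections limit the point:
- The 0.66 is an expectation built from figures the article never combines: 85% and 20% from the study of the Teule criteria, and 6.4% from a meta-analysis. A reader might infer that no bacteraemic control will be found; with a 49% chance of at least one, that does not follow.
- A reader might infer that controls were chosen to lack fever, prostration, respiratory distress and severe anaemia. The documents do not say so. Controls fail a combined rule (abnormal temperature and at least one severity feature), and Sample size determination has them meet the other inclusion criteria. Some or all may be febrile, and some may have a single feature. The 1.32% for all Teule-negative children need not apply exactly to them, and no figure is given for that subgroup. Even expecting five would need a rate of 5/50 = 10%, half the rate assumed in cases.
- Treatment allocation describes the comparator cohort as having non-severe malaria. If that were right, the expected number would more likely be lower.
- The article does not prescribe a contrast of bacteraemic cases with controls, nor commit Phase III to any rule found here. The pooling risk is one the wording leaves open.
- This is an exploratory part of a pilot without a formal sample size.

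**Conclusion.** The point holds in a limited form. Read as improving the sensitivity of the Teule criteria for culture-proven bacteraemia, the stated aim cannot be usefully estimated from this sample. About 0.66 informative children are expected on the protocol's figures (0.55 to 0.74 across its prevalence values) and about 1.3 to 3.1 at an assumed 10% to 15%. The conclusion does not depend on the exact prevalence, because even three such children leave the gain almost undetermined. It does rest on the 85% and 20% applying at this site and on controls resembling Teule-negative children in general.

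The tempting stronger conclusion, that the sub-study as a whole fails, is not supported. Closer targeting among Teule-positive children can still be explored, with moderate precision for specificity and poor precision for sensitivity. A correction should be made, since the text now claims something the design cannot show and leaves open a comparison partly confounded by Teule status.

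**What to change.** 1. In Biomarker and gut barrier function, restate the aim as improving specificity and positive predictive value among Teule-positive children. Make the matching change where the targeting aim is set against the control cohort: hypothesis 2, specific objective (iii), the Discussion and the Abstract.
2. Make bacteraemic versus non-bacteraemic children within the 105 cases (about 21 against 84) the main accuracy analysis, with exact confidence intervals for sensitivity and specificity.
3. Use the 50 controls to describe reference marker distributions and false-positive rates in low-risk children. State that detection of bacteraemia missed by the Teule criteria cannot be usefully estimated.
4. If the sensitivity phrase was meant to refer to infection that blood culture misses, say so and name the molecular reference standard.

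No extra patients or assays are needed. Trial status reports recruitment complete and data under analysis, so the change falls on the analysis and its claims, and enrolling many more Teule-negative children is no longer an option. The cost is a narrower claim for an exploratory sub-study, and controls no longer enlarge the non-bacteraemic denominator.

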## Trial outcome measures

### Primary outcomes

•  Change in CRP, a putative marker of sepsis at 72 hours (continuous) and microbiological cure (seven-day) (binary), alone and as a composite with seven-day survival.

•  The changes in CRP between day 0 and day 3 as the main endpoint for the PKPD studies.

### Secondary outcomes

The secondary outcome measures are:

•  Mortality at 48-hours and longer-term survival (to day 28 and to day 90).

•  Length of hospital stay (days)

•  Re-admission to hospital by 90 days

•  Adverse events

•  The population PK of azithromycin and their relation (combined with pathogen susceptibility) with treatment outcome (PD).

### SAEs and interim analyses

SAEs will be reviewed immediately by a designated physician (SAE reviewer) and reported to the appropriate ethics and regulatory committees within one week. The Chief Investigator will inform the Trial Steering Committee (TSC) and Data Monitoring Committee (DMC) for review on a regular basis (as deemed necessary).

### DMC

An independent DMC (see composition at the end of the protocol) will review data on enrolment, safety, adherence to the trial protocol and efficacy at regular intervals and in strict confidence. The terms are covered in the DMC charter, signed by the chair and trial statistician. There are no fixed ‘stopping rules’. The DMC will receive and review information on the progress and accruing data of the trial and provide advice on the conduct of the trial to the TSC. The DMC would inform the Chair of the TSC if, in their view the results are likely to convince a broad range of clinicians, including those supporting the trial and the general clinical community, that, on balance, one trial arm is clearly indicated or contraindicated for all participants or a particular category of participants. The DMC is comprised of a chair and two other independent members. None declared conflicts of interest.

### Trial monitoring

The Mbale site will use a web enabled trial database and will be responsible for data entry and local trial management. The site will retain the original case report forms (CRFs). Data stored on the database will be checked for missing or unusual values (range checks) and checked for consistency within participants over time. If any such problems are identified, the site will be contacted and asked to verify or correct the entry. Changes will be made on the original CRF and entered into the database at the site. Kilifi Clinical Trial Facility will also send reminders for any overdue and/or missing data with the regular inconsistency reports of errors.

This trial will be monitored according to a monitoring plan which will set out the frequency of visits, the degree of source document verification against the CRFs and the requirements for triggered on-site monitoring visits. This plan will also detail the procedures for review and sign-off. The monitoring will adhere to the principles of ICH GCP.

The site initiation visits will include training in the trial procedures, as well as practical training in administration of trial interventions, reporting guidelines for adverse events of study interventions as well as other trial procedures. All staff at sites involved in the trial will receive formal training in GCP through a dedicated training programme during site initiation visit and will also be required to complete an on-line course. 

The Clinical Trial Facility in Kilifi oversees standards and quality of all trials conducted through the KWTP and through its monitoring systems and standard operating procedures are organised to ensure that all sites can be monitored with equal independence and rigor. All monitors will be appropriately qualified and trained.

At each monitoring visit the monitors will:

▪   verify completeness of Trial Master File

▪   confirm adherence to protocol

▪   review eligibility verification and consent procedures

▪   look for missed clinical event reporting

▪   verify completeness, consistency and accuracy of data being entered on CRFs

▪   evaluate drug accountability

▪   provide additional training as needed

The monitors will require access to all patient medical records including, but not limited to, laboratory test results and prescriptions. The investigator (or delegated deputy) should work with the monitor to ensure that any problems detected are resolved.

